**Design and Methods:**

This two-arm randomized controlled trial will assign 200 participants to a culturally and linguistically tailored web-based sleep educational platform. The website will be developed to ensure that the content is user friendly and that it is readable and acceptable by the target community. Participants will receive login information to a password-protected website and will have access to the website for 2 months. Study assessments will be collected at baseline, 2 months (post-enrollment) and at 6 months (follow-up). We will use qualitative and quantitative methods to develop tailored materials and to ascertain whether tailored materials will increase OSA knowledge and OSA health literacy by comparing blacks exposed to tailored materials versus those exposed to standard sleep health literature. We hypothesize that exposure to tailored OSA information will improve OSA health literacy.

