### Objectives

Despite these limited studies, which have significant implications for the field of sleep medicine, we know of no interventions to improve adherence to treatment for sleep disorders or adherence to physician recommendations for sleep screening among patients with low health literacy. Our primary objective is to develop the Tailored Approach to Sleep Health Education (TASHE) program using a multilevel community-engaged approach. We will use themes ﻿from focus group to develop a culturally and linguistically tailored wbsite and video vignettes. We will incorporate those themes into an interactive website with OSA health content designed for lay people. This website will thus serve as a platform facilitating exchange of information between sleep scientists, community health providers, potential patients, and lay health advisors. We will also seek endorsement of TASHE materials by healthcare providers and stakeholders to ensure their adoption and dissemination. Our secondary objective is to evaluate TASHE’s effectiveness in increasing OSA health literacy among blacks. The main hypotheses for this study are: (1) modifiable barriers (e.g., negative beliefs and attitudes toward sleep, perceived bias in healthcare, inadequate access, and lack of cultural and linguistic tailoring of sleep health materials to blacks) will comprise emergent themes from focus groups; (2) participant engagement will increase acceptability of sleep health messages. Stakeholder engagement will facilitate adoption, dissemination, and sustainability of the program. Provider engagement will enable tailoring of messages addressing patient’s concerns about effectiveness, benefits, and harms of treatment options to inform decision-making; and (3) exposure to tailored OSA health messages will improve OSA health literacy.

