### Control condition

Participants randomized to the control condition will receive an iPad ﻿with﻿ free access to the NSF and NHLBI website via an iPad. Currently, there is no specific comparative effectiveness data evidencing superiority of any website or other format for increasing sleep health literacy. Furthermore, there has been previous research to suggest the overall difficulty that patients experience in using the NSF materials. Thus, our study will ascertain effectiveness of a tailored website compared to the standard websites. Participants in the control condition will have access to the culturally and linguistically tailored sleep informational website at 6 months post-enrollment date.

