### Sample size

Guided by principles governing the use of focus group data, the sample size will be determined when we reach a point of “saturation”, which is when additional group sessions are not likely to produce new themes. Based on previous research [49, 50], we expect that five groups will be sufficient to capture key themes for the project. In the secondary objective - assuming a medium effect size (d = 0.32), as derived from Cohen [51], and a sample size of 200 - the study will be adequately powered (>85%) to detect significant differences between participants likely to show improvement in health literacy scores and those who are not using Fisher’s exact tests (critical X^2^ = 7.98). In a previous pilot study, we found that 40% of black patients in the community adopted recommendations for OSA treatment after exposure to health messages, which compares to 27% who did without such exposure. Assuming a 13% increase in the likelihood of adoption of health messages and a sample size of 200, the proposed study will have adequate power for a preliminary test of the hypothesis that exposure to health messages will foster improvement in sleep health literacy. Achieving the goal of a 13% increase would have an important public health impact. A two-tailed test, with 85% power and α = 0.05 comparing 27% to 40% requires 100 participants per arm [52].

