For aim 3, we will examine which subjective measures are associated with increased OSA health literacy using multivariate logistic regressions. The main dependent measure will be a binary factor: [yes versus no]; candidate predictors are indicated in Table 1. We will use multivariate analysis to explore whether sociodemographic variables (e.g., age, income, education), lifestyle practices (e.g., diet, exercise, smoking, and drinking habits), Internet self-efficacy, and baseline sleep measures (e.g., OSA knowledge, OSA beliefs, and knowledge of sleep hygiene) indexing OSA health literacy improved after exposure to health messages. We assess OSA health literacy with the Sleep Apnea Literacy scale, a 24 -item questionnaire developed by a sleep expert, and expert in scale design. The questionnaire assesses sleep apnea knowledge and sleep apnea clinical management. Sample items include “When breathing stops during sleep this is called sleep apnea” and “Loud snoring can be a sign of sleep apnea.” Ninety-one participants average age 38, and 48% white, 27% African American completed the questionnaire. The questionnaire was developed using exploratory and confirmatory analyses. The questionnaire includes items across three scales, including sleep apnea literacy (component alpha 0.74), sleep apnea self-efficacy (component alpha 0.76), and sleep apnea clinical management (component alpha 0.65). The concurrent scale validity is 0.85. To compare participants who exhibited improvement in health literacy and those who did not 2 months post-enrollment, *t* tests and chi-squared tests will be used. Multivariate analysis of covariance will be used to assess effects of sleep health messages on sleep measures (e.g., OSA knowledge, OSA beliefs, knowledge of sleep hygiene, and S-TOFHLA scores); effects of confounders will be adjusted. Baseline subjective factors will be entered in a linear regression model in order to determine which factors are associated with higher health literacy scores. In post hoc analyses, we will also explore whether combined effects of exposure to tailored web-based content, and video vignettes received through the website had greater impact on improvement in sleep apnea literacy scores.

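### The aim 3 analysis section does not state the comparison of randomised arms on the Sleep Apnea Literacy Scale that the trial's question and per-arm sizing imply

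*Protocol article*

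**What the plan says.** The question is comparative. The abstract describes "comparing blacks exposed to tailored materials versus those exposed to standard sleep health literature". Hypothesis 3 under Objectives is that "exposure to tailored OSA health messages will improve OSA health literacy". The Control condition section adds that "our study will ascertain effectiveness of a tailored website compared to the standard websites". Allocation is 1:1, with 100 per arm.

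The outcome instrument is named under Statistical analysis: "We assess OSA health literacy with the Sleep Apnea Literacy scale".

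The same section describes five analyses for aim 3:

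- Logistic regression on a binary main dependent measure: "we will examine which subjective measures are associated with increased OSA health literacy using multivariate logistic regressions". Candidate predictors are those in Table 1.
- t tests and chi-squared tests, introduced with "To compare participants who exhibited improvement in health literacy and those who did not 2 months post-enrollment".
- MANCOVA: "Multivariate analysis of covariance will be used to assess effects of sleep health messages on sleep measures". The examples given are OSA knowledge, OSA beliefs, sleep hygiene knowledge and S-TOFHLA.
- Linear regression of literacy scores on baseline subjective factors.
- A post hoc look at the combined effect of tailored web content and video vignettes on literacy scores.

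The Sample size section claims power to detect "differences between participants likely to show improvement in health literacy scores and those who are not". It then sizes the trial per arm on 27% versus 40%.

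**The concern.** The effect of tailoring can be read only from a comparison of the arms as randomised. Most of the stated aim 3 analyses ask something else: which participant characteristics go with improvement. Improvement across both arms together can arise from repeat testing, regression to the mean or use of either website, so correlates of improvement do not show what the tailored site added. Improvers and non-improvers are also groups formed after randomisation by the outcome itself, so differences between them are observational. An analyst who followed the section to the letter could finish the logistic, linear, t and chi-squared analyses without estimating the effect that hypothesis 3 is about.

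**Working it through.** The main check is a reading of each stated analysis against two requirements: does it name study arm as the factor, and does it name the Sleep Apnea Literacy Scale (or improvement on it) as the outcome? The bracketed yes/no dependent measure is read here as improved OSA health literacy, yes or no, on that scale.

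1. **Logistic regression.** Outcome: yes, on this reading. Arm: no. Table 1 lists 11 rows of questionnaires and demographic or clinical variables; arm is not among them. One row is the outcome scale itself.
2. **t and chi-squared tests.** Outcome: used to form the groups. Arm: not named as the variable compared. A chi-squared test of improvement by arm would answer hypothesis 3, but the text does not say so. The t tests cannot be that comparison, because with improvement as the grouping they compare a continuous characteristic.
3. **MANCOVA.** Outcome: not named, though the list is introduced as examples. Arm: not named; the factor is sleep health messages. Controls also receive sleep health content, from the NSF and NHLBI websites. S-TOFHLA, which is in the list, measures general health reading and numeracy, not OSA literacy.
4. **Linear regression.** Outcome: literacy scores. Arm: no; baseline factors are entered.
5. **Post hoc analysis.** Outcome: yes. Arm: not stated as a contrast. It concerns components of the tailored site, which the control arm cannot open until 6 months after enrolment.

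None of the five meets both requirements as written.

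The Sample size section gives two contrasts. One is improvers versus non-improvers. The other is exposed versus unexposed, 27% versus 40%, counted per arm. Only the second is a comparison of randomised groups, and the Statistical analysis section follows the first.

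Stating the arm contrast ties the analysis to the power figures, so these were checked. Inputs from the Sample size section: p1 = 0.27, p2 = 0.40, two-sided α = 0.05, power 85%, 100 per arm, d = 0.32.

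- Number per arm = [1.960·√(2·0.335·0.665) + 1.036·√(0.27·0.73 + 0.40·0.60)]² / 0.13² = (1.308 + 0.685)² / 0.0169, which rounds up to 236. The stated 100 is not reproduced.
- Power with 100 per arm = Φ[(0.13·√100 − 1.308) / 0.661] = Φ(−0.0125) = 49.5%. By exact enumeration of Fisher's test it is 43.5%.
- If d = 0.32 is read as a standardised mean difference, power = Φ(0.32·√(100/2) − 1.960) = Φ(0.303) = 61.9%.

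The shortfall in sample size is a separate fault. The present point does not depend on it, but anyone rewriting the contrast will meet it.

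**The case against.** The strongest reply is that an arm comparison is plainly intended and that a journal article need not list model terms. Several parts of this stand:

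- The abstract and the Control condition section state tailored versus standard, and the final sizing sentence is per arm with a stated α.
- The MANCOVA outcomes are examples, so absence of the scale is not exclusion. With one arm given tailored messages and the other standard websites, an effect of messages plausibly means an arm effect.
- A chi-squared test is symmetric, so comparing improvers with non-improvers on arm is the same test as comparing arms on improvement.
- The post hoc sentence does link exposure with literacy scores.

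A reader might therefore infer too much from the section: that the trial will discard randomisation, that no arm comparison on literacy will be made, or that the MANCOVA rules the scale out. The documents do not support any of these.

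The appeal to detail left for a fuller plan does not stand. The article does not stay silent on aim 3. It names a main dependent measure, the source of its predictors and the groups to be compared, and it points them at a different question. The instrument assigned to the hypothesis 3 outcome should not have to be inferred from an open list of other outcomes.

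**Conclusion.** The point holds as a mismatch within the document. The Statistical analysis section does not state the randomised-arm contrast on the Sleep Apnea Literacy Scale that the abstract, hypothesis 3, the Control condition section and the per-arm sizing imply. The logistic, linear, t and chi-squared analyses are worded as predictor searches or comparisons of improvers with non-improvers. The MANCOVA is ambiguous on both factor and outcome, and the remaining analysis is post hoc. This should be corrected before analysis, because hypothesis 3 otherwise has no explicitly stated test.

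No numerical bias is claimed; the consequence depends on how the analyst reads the section. The conclusion rests on two readings: that the binary dependent measure means improved OSA health literacy, and that Table 1 defines the candidate predictors as the text says.

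**What to change.** - State as the main aim 3 analysis the comparison of tailored versus control arm, all participants as randomised, on Sleep Apnea Literacy Scale improvement at 2 months. This keeps the stated binary measure. Put arm in the logistic model and report its effect with a 95% CI.
- Add a baseline-adjusted comparison of the 2-month score by arm as a supporting analysis. It could be the main one instead, but only if the power statement is rewritten to match.
- In the MANCOVA, name arm as the factor and say whether the scale is among the outcomes.
- Label the improver versus non-improver tests and the predictor regressions exploratory.
- In the Sample size section, replace the improver versus non-improver wording with the arm contrast.

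Table 1 already schedules the scale at baseline, 2 and 6 months, so no new data are needed. With the binary measure kept, the cost is a change of wording. Making the score the main outcome would also change the endpoint and its power basis. Either way the power figures should be revisited: 100 per arm gives about 50% for 27% versus 40% and about 62% for d = 0.32, against the stated 85%.

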## Data monitoring

In compliance with NIH requirements, we will establish a data safety and monitoring plan (DSMP). The purpose of the DSMP is to ensure the safety of participants and the validity and integrity of the data. In adherence to NIH policy regarding data sharing, the DSMP will be tasked to develop its data-sharing plan in consultation with an external representative. Data will be made available from the institutions’ website once the main findings of the project have been published. The plan will incorporate language to ensure that the rights and privacy of people who participate in NIH-sponsored research are protected at all times. Thus, data will be free of identifiers that would permit linkages to individual research participants and variables that could lead to deductive disclosure of individual participants. The DSMP internal committee will review all requests for data before access to the data is granted.

## Discussion

OSA is one of the most commonly diagnosed sleep disorders that disproportionately affect blacks. With the rapidly changing field of sleep medicine, including the use of home-based sleep studies, patients may require assistance navigating sleep health services [55]. In addition, there are various treatment options, although CPAP is the most effective. Moreover, treatment for OSA is efficacious and can reduce symptoms of co-morbid health conditions including CVD, diabetes, and hypertension. Unfortunately, adherence to treatment for OSA remains suboptimal and blacks in particular may use CPAP far less than their white counterparts, thus limiting their ability to benefit from treatment. Although several factors have been proposed as contributing to poor adherence, including machine difficulties and psychosocial factors, few studies have explored the role of health literacy [19, 55]. Limited health literacy is associated with several health outcomes and requires a complex set of skills. Thus, it is plausible that individuals with limited OSA health literacy would benefit from the intervention, which will utilize a web-based approach to increase OSA health literacy that we are testing.

In conclusion, there is growing interest in using telehealth among minorities [56–58]. Studies are beginning to show that Internet use in minority communities has increased over the last several years. A random-digit telephone survey of New York residents found that 77% had computer access and 65% used the Internet [59]. Online information affects health habits of New York minorities, with 47% in a telephone survey stating it changed their exercise routines and 44%, their eating habits [60]. Computer-based pre-screening is well accepted for HIV testing, with 80% of respondents in one study preferring the computer-based screening compared to other methods [61]. Thus, we believe that an approach that builds on what is now known about the potential role of web-based information might be an effective means to increase OSA knowledge and OSA health literacy, thereby increasing utilization of sleep-related services among blacks.

### Trial status

Recruiting.

## Abbreviations

AASM: American Academy of Sleep Medicine
ABS: Apnea Beliefs Scale
AKT: Apnea Knowledge Test
ARES: Apnea Risk Evaluation System
PAP: Positive airway pressure
CSC: Community Steering Committee
CVD: cardiovascular disease
DM: diabetes mellitus
DSMP: data safety and monitoring plan
FAB: Faculty Advisory Board
HTN: hypertension
IRB: Institutional Review Board
NHLBI: National Heart, Lung, and Blood Institute
NIH: National Institute of Health
NSF: National Sleep Foundation
OSA: Obstructive Sleep Apnea
PI: Principal Investigator
S-TOFHLA: Short Test of Functional Health Literacy in Adults
RA: Research Assistant
TASHE: Tailored Approach to Sleep Health Education
